### Eligibility criteria

All patients admitted to the hospital with an acute stroke are screened for eligibility. Patients with severe strokes and those who cannot walk independently are not eligible for the study. As it is a pilot study and because we are interested in feasibility of the study concept, the inclusion criteria are set very broad. We also included patients who would likely have difficulty operating the smartwatch.

### Inclusion criteria for the study:

ischemic strokeinitial NIHSS or NIHSS determined at the moment of maximal deterioration 1–18age >= 18 yearspre-stroke independencesufficient motivation to exercise regularly

### Exclusion criteria:

transient ischemic attackpremorbid motor disability, musculoskeletal disease impairing degree of movementbalance and transfer function which requires assistancecardiac disease not allowing to perform aerobic trainingpsychiatric disordersinability to give informed consent

### Randomization

We used a computer-generated randomization sequence for 30 patients (https://www.randomizer.org/). This sequence was kept by a study assistance. After inclusion, group allocation was disclosed. After that, all researchers and the patients were aware of group allocation throughout the study process.

### Outcome measures

All assessments are performed at baseline and final assessment after 90 days.

Motor function is measured by the Fugl Meyer-assessment (FMA) for the upper extremity (UE) and the lower extremity (LE) at baseline and final assessment. The FMA-UE is measured in a score with a maximum of 66 for motor function, the FMA-LE reaches a sum score of 34 for motor function. In addition, we will perform the 6-min walk test.

An overall cognitive screening was performed using the MoCA, scores range from 0 to 30. Psychomotor speed was assessed via the SDMT (scores 0–100) in the oral test version. The FSMC (scores 20–100), the HADS-D (score 0–52) and the WHODAS 2.0, 12-item-version (scores 0–48) were administered as self-report questionnaires. All neuropsychological measures were collected in a face-to-face manner by trained personnel. Where possible, a parallel version was used for the 3-month follow-up visit.

To characterize immunological changes, we perform flow cytometry analysis of cryo-asservated peripheral blood mononuclear cells and sera. In our analysis, we focus on the major leukocyte subtypes, effector functions such as cytokine production, cytolytic activity, differentiation and activation levels, and expression of regulatory molecules. A major readout will be comparison of changes in the immune cell profiles between the interventional and control group.

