### Role of the immune system in stroke rehabilitation

The ischemic event in the brain induces a neuroinflammatory process. The excessive activation of the autonomic system causes an immunodepression correlating with a lymphopenia and dysfunctional immune cells. Local immune responses and a local sustained inflammation in the brain, such as formation of neutrophil extracellular traps at the borders of the infarct zone, contribute to further neurological deterioration in the subacute and chronic phase [9, 10]. Anti-inflammatory and neuroprotective treatments in the acute and subacute phase are being investigated, but none of them has proven to be effective yet. In general, the anti-inflammatory effects of regular moderate exercise by affection of the immune regulation are well-known [18]. Regular endurance training changes the phenotype of neutrophils to one which resembles a more anti-inflammatory phenotype. Similar effects are described for monocytes, which differentiate more into the non-classical, less inflammatory phenotype upon regular exercise. Regarding the adaptive immunity, it is known that exercise improves regulatory T-cell-function and –numbers [18].

Taking into account the correlation and assumed contribution of a chronic low-grade inflammatory state to typical lifestyle-associated and cardiovascular diseases and the potential of physical activity to modulate the inflammatory state [18], physical activity might be a link to complement direct treatment of typical stroke consequences.

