### Sample size

30 patients will be included in the study. As we perform the first trial to translate our experimental findings into the clinic, no a priori sample size calculation has been performed.

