### Statistical analysis

We aim to perform a simple linear regression analysis using the averaged amount of exercise as predictor and measurements on day 90 of each test variable as outcome. Baseline measurements and other possible nuisance variables will be included as additional covariates. As prior analyses, we will analyse the amount of exercise across both groups.

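### The immune group comparison is stated as a comparison of changes with no baseline adjustment attached, and is not reconciled with the exercise-amount regression in the statistical section

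*Protocol article*

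**What the plan says.** The Outcome measures section closes its account of the flow-cytometry work with: "A major readout will be comparison of changes in the immune cell profiles between the interventional and control group". The contrast is between the two randomised groups and the quantity compared is change. No model is named, and nothing is said for or against baseline adjustment. The same section makes both measurements available: "All assessments are performed at baseline and final assessment after 90 days".

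The Statistical analysis section gives the only model in the article, a "simple linear regression analysis using the averaged amount of exercise as predictor and measurements on day 90 of each test variable as outcome". It continues: "Baseline measurements and other possible nuisance variables will be included as additional covariates". The one analysis there that involves the two groups concerns exposure, not outcome: "As prior analyses, we will analyse the amount of exercise across both groups". Immune variables are neither named nor excluded.

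On size, the Sample size section says "30 patients will be included in the study" and that "no a priori sample size calculation has been performed". The Randomization section gives no allocation ratio.

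**The concern.** The two sections differ in two ways for the immune data. One concerns the form of the outcome: change in one place, the day-90 value given baseline in the other. The other concerns the contrast: randomised group in one place, amount of exercise performed in the other. The baseline covariate belongs to the exercise model, so no sentence attaches it to the group comparison. An analyst who follows the Outcome measures sentence literally would subtract baseline from day 90 and compare the group means.

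That subtraction fixes the slope of day 90 on baseline at 1. If the true slope is lower, the comparison is noisier than it need be. A group that starts high by chance will then tend to show a smaller change whether or not training does anything. Baseline is taken early: enrolment is within 14 days of the stroke, and the introduction says of the post-stroke period that "The excessive activation of the autonomic system causes an immunodepression correlating with a lymphopenia and dysfunctional immune cells". Day 90 may be a different immune state, which makes a slope near 1 less plausible, though the article gives no figure.

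Immunological effects are among the stated objectives, and the trial is small enough for chance imbalance on individual markers to be common.

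**Working it through.** The plan gives no power, SD or correlation, so it has no figure to reproduce. The check asks what an unadjusted comparison of changes would cost relative to baseline adjustment.

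**Inputs**
- Total N = 30 (Sample size section), all assumed to be analysed.
- Assumed: 15 per arm, because the ratio is not stated.
- Assumed: equal SD at baseline and day 90, set to 1.
- Assumed: correlation rho between baseline and day 90, from 0.3 to 0.95.

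**Variance**
1. Per-patient variance of a change: 2(1 − rho).
2. Per-patient residual variance after baseline adjustment (ANCOVA): 1 − rho².
3. Ratio: (1 − rho²) / [2(1 − rho)] = (1 + rho)/2.
4. Estimating the slope at N = 30 inflates the ANCOVA variance by 1 + 1/26 = 27/26 = 1.038.

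**Imbalance**
1. Standard error of the baseline difference: sqrt(2/15) = 0.365 SD.
2. Given a baseline difference B, the change contrast is expected to be off by −(1 − rho)B, and the ANCOVA contrast by about 0.
3. Chance that the baseline difference on one marker exceeds 0.5 SD in either direction: 0.5/0.365 = 1.37 standard errors, two-sided probability 0.17.

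| rho | (1 + rho)/2 | × 27/26 | Shift of change contrast from a 0.365 SD imbalance |
|---|---|---|---|
| 0.3 | 0.65 | 0.68 | 0.70 × 0.365 = 0.26 SD |
| 0.5 | 0.75 | 0.78 | 0.50 × 0.365 = 0.18 SD |
| 0.7 | 0.85 | 0.88 | 0.30 × 0.365 = 0.11 SD |
| 0.9 | 0.95 | 0.99 | 0.10 × 0.365 = 0.04 SD |
| 0.95 | 0.975 | 1.01 | 0.05 × 0.365 = 0.02 SD |

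The shift is opposite in sign to the imbalance.

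**Simulation** (10,000 trials per rho)
- Variance ratios were 0.67, 0.79, 0.89, 0.98 and 1.01, in line with the table.
- The change estimate correlated with the baseline imbalance at −0.59 (rho 0.3), falling in size to −0.23 (rho 0.9). The ANCOVA estimate did not correlate with it.
- The mean error of both estimators was about 0. The imbalance effect is therefore conditional on the imbalance that occurs and is not a systematic bias.
- Regressing the change on group with baseline as covariate gave the same group estimate as regressing the day-90 value, to rounding error. Comparing changes is therefore harmful only when baseline is left out.

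**Equal SDs.** The direction does not depend on this assumption. With slope b of day 90 on baseline, Var(change) = Var(residual) + (1 − b)² × Var(baseline). Apart from the 27/26 factor, adjustment cannot do worse.

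**The case against.** The strongest reply is that the protocol never specifies an unadjusted analysis. The sentence sits under Outcome measures and names what is of interest. The statistical section covers each test variable and adjusts for baseline, so the two may be read together as an adjusted comparison of changes, which would lose nothing. An article may also leave the model for a broad flow-cytometry panel to the full plan.

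Part of this stands. A reader might infer that the protocol commits to raw change scores, but it does not say so, and a comparison of changes is compatible with ANCOVA. The statistical section does not settle the matter, however. Its predictor is exercise amount, so even if it covers the immune variables it contains no adjusted comparison of the randomised groups. The point is that two stated analyses do not meet. It is not a complaint that model detail is absent.

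Three further limits are fair:
- The gain depends on a correlation that the article does not give, and it disappears at about 0.9 and above.
- A reader might infer from the account of post-stroke immunodepression that the slope must be well below 1. That account gives no data on rebound by baseline level, so it makes a low slope plausible and no more.
- This is a pilot without a sample size calculation, and no decision rule rests on the immune result.

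**Conclusion.** The point holds in a limited form. The immune readout is described as a between-group comparison of changes with no baseline adjustment stated. The only baseline-adjusted model has exercise amount as predictor, and the two are not reconciled.

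If the changes are analysed unadjusted, baseline adjustment would cut the variance by about 12% to 32% for correlations of 0.7 down to 0.3. It would gain about 1% at 0.9 and lose about 1% at 0.95. These figures rest on 15 per arm, equal SDs and the assumed correlations. The imbalance shifts of 0.04 to 0.26 SD (correlations 0.9 to 0.3) apply to a trial whose baseline difference happens to be one standard error.

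Two stronger conclusions are not supported. The first is that the change comparison is biased: over randomisations it is not. The second is that applying the statistical section's model to the immune data would repair the comparison: it would replace the randomised contrast with one on exercise actually done, which is not randomised.

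Severity is modest. Confidence is high in the algebra and medium overall, because the text leaves the adjustment open.

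**What to change.** In Outcome measures, state that each immune readout is compared between groups by regressing the day-90 value (log scale where skewed) on randomised group with the baseline value as covariate. The adjusted group difference should be reported with its confidence interval.

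In Statistical analysis, state that this randomised-group comparison is separate from the regression on amount of exercise, and that the latter is not a randomised contrast.

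The cost is wording and one degree of freedom per model. Baseline and day-90 blood samples are already planned. At a correlation of 0.95 the adjusted estimate has about 1% more variance. Under equal SDs the loss stays below the 27/26 factor, that is, below about 4%.

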### Magnetic resonance imaging and spectroscopy

Magnetic resonance imaging (MRI) and spectroscopy (MRS) are conducted to reveal structural and metabolic changes following motor therapy. Specifically, tissue structural changes pre and post therapy will be compared via diffusion weighted imaging (DWI) and subsequent fibre tracking. ^1^H-NMR spectroscopy, localized in the stroke area, should reveal metabolic changes between the scan dates. An advantage of all MRI and MRS techniques is the multitude of information that can be derived from single scan sessions. The following is but an excerpt of possible analyses building on the given acquisition scheme, enabling further analyses if new scientific questions arise down the line. Proposed examples for further analyses are given below.

DWI is acquired with a grid-sampled multi-band EPI sequence, using 101 grid elements (vectors) and b-values up to 4000 s/mm^2^. This allows for beyond-tensor modelling of diffusion, in this case generalized q-sampling imaging [20]. Stroke areas will be identified from hyperintense areas in the DWI or a separate T2-weighted FLAIR (fluid-attenuated inversion recovery) sequence, commonly reflecting local edema. Diffusivity parameters in this area, such as mean diffusivity and diffusion anisotropy, can reveal direct information on structural integrity pre and post treatment and can give insight into local tissue remodelling. Deterministic fibre tracking will further uncover larger scale structural white matter changes: Specific interest will be given to fibre tracks extending from the stroke area or those linking affected brain areas across the corpus callosum or via cortico-spinal tracts. Reconstructed tracks will be analysed for fibre count, 3D extent and along-track diffusivity parameters. Further potential analyses could include intraindividual white matter remodelling not confined to or directly associated with the stroke area. Given an atlas registration, these would even enable group comparisons and correlational tractography.

Localized NMR spectroscopy will reveal the metabolic profile in the stroke area, allowing the study of in situ cellular processes and metabolic conditions. For example, the presence of lactate in the metabolic profile is indicative of anaerobic conditions in the ischemic region, while a decrease in N-acetyl aspartate (NAA) is a sign of acute neuronal damage [17]. Since NMR spectroscopy provides an overview of further metabolites, for example choline-containing compounds, profile analyses may not be confined to lactate and NAA. NMR spectra from the stroke region will be compared to the contralateral healthy area to account for different intra- and interindividual baseline values (Fig. 2).

**Fig. 2 Fig2:**
[figure not shown]
Example images of MRI fibre tracking. The stroke region is highlighted. Left: Colour-coded fibre tracks passing the midline corpus callosum. Right: Corpus callosum fibre tracks are shown in yellow, blue tracks were seeded from the stroke lesion

### Sample size

30 patients will be included in the study. As we perform the first trial to translate our experimental findings into the clinic, no a priori sample size calculation has been performed.

### Statistical analysis

We aim to perform a simple linear regression analysis using the averaged amount of exercise as predictor and measurements on day 90 of each test variable as outcome. Baseline measurements and other possible nuisance variables will be included as additional covariates. As prior analyses, we will analyse the amount of exercise across both groups.

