**Methods:**

Adults with mild to moderate stroke impairment (initial NIHSS or NIHSS determined at the moment of maximal deterioration 1–18) are recruited within two weeks of stroke onset. Study participants must be able to walk independently without risk of falling. All patients are equipped with wearable devices (smartwatches) measuring the heart rate and daily step count. The optimal heart rate zone is determined by lactate ergometry at baseline. Patients are randomized to the control or the intervention group, the latter performing a heart rate-controlled walking training on own initiative 5 times a week for 45 min. All patients receive medical care and stroke rehabilitation to the usual standard of care. The following assessments are conducted at baseline and after 90 days: Fugl Meyer-assessment for the upper and lower extremity, 6 min-walk test, neuropsychological assessment (cognition: MoCA, SDMT; fatigue and depression: FSMC, HADS-D, participation: WHODAS 2.0 12-items), blood testing (i.e. immune profiling to obtain insights into phenotype and functional features of distinct immune-cell subsets) and cranial magnetic resonance imaging (MRI) with grid-sampled diffusion weighted imaging, white matter fibre tracking and MR spectroscopy.

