### Weaknesses

The study requires a high motivation by the participants. Adherence to physical activity without direct reward represents a major challenge. One risk of our study is to include preferentially patients with a high premorbid activity level. We tried to minimize this risk by broad inclusion criteria and setting an individual heart rate zone target. Nevertheless, we cannot adjust for the level of activity patients had before the stroke. Another problem is the operation of the wearable device/smartwatch. Especially older patients face trouble with it and were not able to document their daily activity. Another common challenge for investigating the effects in stroke patients suffering from mild to moderate symptoms is that it is difficult to show the effect. Our sample size is not sufficient to meet this challenge, but we aim to show feasibility of the design to translate the project into larger cohorts.

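### The only outcome model stated for this randomised pilot regresses day-90 scores on the exercise patients actually did, with no term for randomised arm, so its slope is observational and likely to favour exercise

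*Protocol article*

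**What the plan says.** The Abstract (Methods) states: "Patients are randomized to the control or the intervention group". The Randomization section adds: "We used a computer-generated randomization sequence for 30 patients". It also says the trial is open after allocation: "all researchers and the patients were aware of group allocation throughout the study process". Aims of the trial words the objective causally, as the effect of walking exercise on motor function, cognition, fatigue, depression and immune measures. It adds a further aim, conditional on patients benefiting, of estimating how much exercise to recommend.

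The Statistical analysis section then names a "simple linear regression analysis using the averaged amount of exercise as predictor and measurements on day 90 of each test variable as outcome". On covariates it says: "Baseline measurements and other possible nuisance variables will be included as additional covariates". The two groups enter that section only once: "As prior analyses, we will analyse the amount of exercise across both groups".

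Outside that section, one outcome comparison by arm is announced, without a model: "A major readout will be comparison of changes in the immune cell profiles between the interventional and control group".

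Three further statements bear on the predictor:
- Study description and design says patients carry out the training by themselves.
- Arms and interventions says they log it on paper.
- Weaknesses says "Nevertheless, we cannot adjust for the level of activity patients had before the stroke", and reports that some older patients could not record their activity.

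**The concern.** The amount of exercise done over 90 days is settled after randomisation, largely by the patient. It depends on recovery, mood, fatigue, motivation and earlier fitness, and each of these can also move the day-90 scores. Causation can run the other way too: a patient who becomes depressed or fatigued walks less. The article's own introduction describes such a loop between deconditioning and inactivity.

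Randomisation balances these influences in expectation between the arms. It does not balance them between patients who walked much and patients who walked little. A model with exercise amount as predictor and no arm term thus gives up that protection for motor function, cognition, fatigue, depression and participation. The slope could then be reported as the effect of walking when part or all of it reflects who was able to walk.

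**Working it through.** **Nothing to reproduce.** The article states 30 patients without a calculation and gives no effect size, SD or error rate. The check is therefore a comparison of the passages, followed by an illustration with assumed inputs.

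**Step 1: the passages side by side.**

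| Element | What the article states |
|---|---|
| Assignment | randomised, two arms, 30 patients |
| Objective | effect of walking exercise |
| Predictor in the outcome model | averaged exercise actually done |
| Covariates | baseline and unnamed nuisance variables; arm not named |
| Role of arm in the analysis section | describing exercise amount only |
| Outcomes compared by arm | immune profiles only, no model given |
| Admitted unadjusted factor | pre-stroke activity |

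The predictor and outcome are specified positively. The problem is what is fixed, not detail left to another document.

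**Step 2: size of the spurious slope.** All inputs are assumed: 15 per arm, true exercise effect zero, exercise with within-arm SD 1, arms differing by d in mean exercise. A hidden factor U has correlation g with exercise within arm and h with the baseline-adjusted outcome. If U is independent of baseline, the expected slope, in residual SD of the outcome per within-arm SD of exercise, is

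slope = g·h / (1 + d²/4).

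- g = h = 0.3, d = 1.5: 0.09 / 1.5625 = 0.058
- g = h = 0.5, d = 0.5: 0.25 / 1.0625 = 0.235
- g = 0: 0

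Simulation (5000 trials per setting) gave mean slopes of 0.057 to 0.233, in agreement. The formula contains no sample size, so more patients narrow the interval around the wrong value and do not move it.

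**Step 3: false-positive rate in that setting.** At two-sided 5%, over g and h of 0.3 to 0.5 and d of 0.5 to 1.5, the exercise regression rejected in 6.3% to 24.4% of trials. ANCOVA by arm rejected in 4.3% to 5.7%.

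**Step 4: does adjusting for baseline rescue the model?** In a second simulation U correlates 0.5 with the baseline score and has coefficient 0.4 on the day-90 score, so baseline absorbs part of U. Both models adjust for baseline; 5000 trials per cell.

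| g | d | Mean slope | Exercise regression rejects | ANCOVA by arm rejects |
|---|---|---|---|---|
| 0 | 0.5 / 1 / 2 | 0.002 / -0.002 / 0.002 | 5.3% / 5.2% / 5.6% | 4.9% / 5.2% / 5.7% |
| 0.3 | 0.5 / 1 / 2 | 0.084 / 0.074 / 0.045 | 9.7% / 8.7% / 7.1% | 4.8% / 5.0% / 4.6% |
| 0.5 | 0.5 / 1 / 2 | 0.147 / 0.125 / 0.073 | 19.7% / 18.0% / 12.2% | 4.9% / 5.2% / 4.5% |
| 0.7 | 0.5 / 1 / 2 | 0.222 / 0.186 / 0.109 | 38.7% / 32.9% / 21.1% | 4.8% / 4.5% / 5.5% |

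Baseline leaves 1 - 0.5² = 0.75 of the variance of U, so the expected slope is 0.4·0.75·g / (1 - 0.25g² + d²/4). For g = 0.5 and d = 0.5 this is 0.15 / 1.0 = 0.15, against 0.147 simulated. For g of 0.3 or more, nearly all false positives favoured exercise. The bias falls as the arms separate further in exercise done, but it does not vanish.

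**Step 5: what the arm comparison can deliver.** Assume 15 per arm, all with day-90 values.

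- 95% CI half-width, unadjusted: 2.048 × √(2/15) = 2.048 × 0.365 = 0.75 SD
- Difference detectable with 80% power: (1.960 + 0.842) × 0.365 = 1.02 SD
- The same with an assumed baseline-to-day-90 correlation of 0.6: 1.02 × √(1 - 0.36) = 0.82 SD

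**The case against.** **The model is adjusted.** Baseline values are covariates, and those measured include depression, fatigue, walking distance and motor scores. The nuisance clause is open enough to admit others. This stands in part: it reduces the bias, and nobody should read the model as unadjusted. It cannot capture recovery, mood or motivation after baseline, and pre-stroke activity is conceded to be out of reach.

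**A dose analysis serves a stated aim.** This is true of the aim of how much exercise to recommend. That aim is conditional on patients benefiting, which the randomised contrast has to address first. The dose analysis belongs in the plan, but not as the only outcome model.

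**This is a pilot that disclaims power.** Weaknesses says the sample is too small to show an effect and that feasibility is the goal, and no efficacy decision is tied to the regression. This limits the consequences. It argues for wide intervals and modest claims, not for an observational estimate in place of the randomised one.

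**Three stronger readings are tempting and not supported:**
- That randomisation is discarded altogether. Immune profiles are to be compared between arms, and exercise amount is to be analysed across them.
- That the regression is bound to make exercise look effective. With g = 0 there is no inflation, and at the low end of the assumed range the rate is close to nominal.
- That the same bias will pass into a later, larger trial. The bias does not shrink with sample size, but nothing says a later trial would reuse this model.

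**The article is condensed.** Models by arm may exist in a fuller document. That would not change the fact that the article names this model for each test variable.

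**Conclusion.** The point holds. For a randomised trial with a causal objective, the article fixes a patient-chosen, post-randomisation exposure as predictor of each day-90 measure and gives arm no place in that model. The slope is an observational association, likely though not certain to favour exercise.

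The size rests on assumptions, since the documents give no correlation, no separation in exercise and no allocation ratio. With hidden-factor correlations of 0.3 to 0.5 with exercise and with outcome, false significance is roughly 6% to 25%. A comparison by arm stays at about 5%. That 5% supposes that knowing the allocation does not itself shift scores. With open allocation and self-report questionnaires, the arm comparison could still carry reporting bias, though not confounding by exercise chosen.

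**What to change.** Make the main analysis of each outcome an ANCOVA of the day-90 value on randomised arm and the baseline value of the same measure. Include every randomised patient who has a day-90 value, in the arm assigned and whatever exercise was done. Report the adjusted difference with its 95% CI and make no efficacy claim at 30 patients. Patients without an activity record stay in this analysis, whereas they would drop out of the exercise regression.

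Keep the exercise-amount regression, labelled exploratory and observational, for the aim of how much exercise to recommend. State how missing activity records are handled there.

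The cost is a rewritten paragraph and one extra model per outcome, with no new patients or visits. The downside is real: the arm contrast is imprecise at this size, and it is diluted if control patients also exercise.

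Two additions are better left out or heavily caveated:
- *Arm as an instrument for dose.* The first-stage noncentrality is d² × (15 × 15)/30 = 7.5d², or 1.9, 7.5 and 16.9 for d of 0.5, 1.0 and 1.5. The instrument is weak over much of that range. With open allocation, arm may also affect scores by routes other than exercise.
- *A new question on pre-stroke activity.* Recruitment began in October 2022, so patients already enrolled would be answering from late recall.
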